## Abstract

**Background:**

Endovenous treatment of varicose veins has increased in popularity over the last decade. There remains, however, a degree of uncertainty regarding the role of compression bandaging or hosiery following this intervention. The National Institute for Clinical Excellence Guideline Development Group has advocated further research to evaluate the clinical and cost-effectiveness of this post-procedure intervention. In addition to this, the duration of compression bandaging also warrants clarification.

**Methods:**

Ethical approval for the study was obtained from the Singhealth Centralised Institutional Review Board (CIRB Ref: 2017/2710). Consent to enter the study will be sought from each participant only after a full explanation has been given, an information leaflet offered and time allowed for consideration. Signed participant consent will be obtained. Patients will be randomised to either compression (group A) or no compression (group B). The primary aim of the study is to assess the patient’s pain scores for the first 10 days post procedure using a visual analogue scale. Secondary aims include an assessment of patient compliance with compression, quality of life scores, clinical effectiveness, rates of bruising and phlebitis, time taken to return to normal activities, patient satisfaction and occlusion rate at 6 months.

**Discussion:**

The purpose of this study is to examine the effect of compression therapy in patients having mechano-chemical ablation (MOCA) therapy for truncal incompetence of their varicose veins using the ClariVein® device. This study may provide clarification on the role of compression therapy in patients undergoing MOCA.

**Trial registration:**

ClinicalTrials.gov, NCT03685838. Registered on 26 September 2018.

## Background

Varicose veins are common and are known to affect approximately one-third of the population [1]. Chronic venous disease (CVD) has been shown to have a negative impact on the quality of life of patients and treatment of varicose veins has been demonstrated to lead to improvement in quality of life [2–4]. Over the past decade, new endovenous techniques have been introduced and these are felt to be cost-effective, especially when performed in an outpatient or ‘office-based’ setting [5]. There is currently uncertainty about the use of compression stockings following treatment of varicose veins. In their consensus statement in 2008, the International Union of Phlebology (IUP) stated that there is good evidence for using compression in certain clinical indications [6]. These include the management of telangiectasia after sclerotherapy, varicose veins in pregnancy, prevention of thromboembolism and healing of ulcers. However, a few questions remain unanswered, such as the length of treatment and level of compression to be used [6]. The Society for Vascular Surgery and the American Venous Forum recommend using compression stockings post-operatively for 1 week to prevent haematoma formation, pain and swelling [7]. The 2013 NICE Guidelines on Varicose Veins in the Legs recommended that compression hosiery is used for no more than 7 days after interventional treatment for varicose veins [8]. However, due to current uncertainty of compression bandaging or hosiery compared to no compression after interventional treatment for varicose veins, the NICE Guideline Development Group has advocated further research to evaluate the clinical and cost effectiveness of this post-procedure intervention [8]. The guidelines also suggested looking into the length of time compression bandaging should be worn if it is shown to be beneficial [8].

Several researchers have looked into the practice of using compression after venous ablation. In a survey of the management of varicose veins by the members of the Vascular Society of Great Britain and Ireland, Edwards et al. [9] found that the majority of surgeons used bandages post-operatively, with 49% using elastic bandages. The literature on the use of compression stockings following treatment of varicose vein is limited.

Between December 2006 and February 2008, Bakker et al. [10] conducted a prospective randomised controlled trial on the use of compression stockings after endovenous laser ablation of the great saphenous vein. One hundred and nine patients were approached, with 93 finally randomised to use compression stockings for 2 days (Group A) and 7 days (Group B), respectively. All patients were followed up for 3 months post treatment and the visual analogue scale (VAS) for pain was recorded at 48 h, 1 week and 6 weeks. A physical examination and quality of life were assessed at 1 week and 6 weeks. The occlusion rate at the 3-month point was also evaluated. Physical function and vitality were shown to be significantly better in group B at 1 week follow-up, but there was no statistically significant difference at 6 weeks. At 1 week, it was also noted that the VAS score in group B (VAS score 2.0 ± 1.1) was significantly lower than in patients wearing compression stockings for 48 h (VAS score 3.7 ± 2.1) (*p* ≤ 0.001) [10]. No significant difference, however, was observed at 6 weeks post procedure. Limitations of the study include the high drop-out of the trial (40 out of the initial 109 approached) and the absence of any phlebectomies or sclerotherapy in the patients.

Elderman et al. [11] carried out a randomised trial to assess the effect of compression stockings after endovenous laser therapy (EVLT) for great saphenous vein incompetence. Patients’ reported pain scores and quality of life scores were evaluated on the day of the procedure, 2–3 days afterwards and 2–6 weeks post procedure. A total of 111 patients were randomised to stockings (*n* = 55) and no stockings (*n* = 56). There was a statistically significant difference in the pain scores in favour of the stockings group up to day 7, but this difference was no longer present by week 6. There was also a greater use of analgesia in patients in the no stockings group compared to patients wearing stockings (*p* < 0.05). In addition, patients wearing stockings reported a statistically significantly higher score of satisfaction at 2 days (4.44 vs 4.15) and at 6 weeks (4.59 vs 4.18). The absolute difference, however, was small. Two notable limitations of the study were the high level of dropouts (16 from each group) and the absence of any blinding.

Hamel-Desnos et al. [12] undertook a randomised controlled trial looking at the effect of compression in patients receiving foam sclerotherapy of the saphenous vein. They noted that patients with compression had similar pain and quality of life scores to patients not wearing any compression. They concluded that additional use of compression had no impact on the effectiveness of obliteration of veins, satisfaction scores, symptoms and quality of life, and that further controlled trials were needed to answer the question of whether using compression results in any difference to the outcome of varicose vein procedures. A summary of the available evidence is presented in Table 1.

**Table 1 Tab1:** Summary of published studies related to the COMMOCA trial

Author	Study arms	Number of patients (*n*)	Timeframe	Outcomes	Limitations
Bakker et al. [10]	Compression × 2 days (Group A) vs compression × 5 days (Group B)	93 patients randomised to stockings (*n* = 48) and no stockings (*n* = 45)	Pain scores recorded using VAS at 48 h, 1 week and 6 weeks. Total follow-up of 3 months	Physical function and vitality significantly better in group B at 1 week. No statistically significant difference at 6 weeks. VAS score in group B (2.0 ± 1.1) was significantly lower at 1 week than in group A (3.7 ± 2.1, *p* ≤ 0.001) [10]. No significant difference, observed at 6 weeks post procedure	High drop-out of the trial Absence of any phlebectomies or sclerotherapy
Elderman et al. [11]	Stockings vs no stockings	111 patients randomised to stockings (*n* = 55) and no stockings (*n* = 56)	Pain scores and quality of life scores evaluated on the day of the procedure, 2–3 days afterwards and 2–6 weeks post procedure	Statistically significant difference in the pain scores in favour of the stockings group up to day 7. No significant difference at 6 weeks Greater use of analgesia in patients in the no stockings group (*p* < 0.05). Significantly higher satisfaction scores in stockings group at 2 days (4.44 vs 4.15) and at 6 weeks (4.59 vs 4.18)	High level of dropouts and the absence of blinding
Hamel-Desnos et al. [12]	Compression vs no compression	60 patients randomised to compression (*n* = 31) vs no compression (*n* = 29)	Clinical and duplex ultrasound assessments made on days 14 and 28 post procedure	No difference between compression and control groups when comparing efficacy, side effects, satisfaction scores, symptoms and QOL	Poor compliance with compression therapy

*COMMOCA* COMpression Therapy Following MechanO-Chemical Ablation, *QOL* quality of life; *VAS* visual analogue scale

Mechano-chemical ablation (MOCA) combines mechanical damage to the endothelium caused by a rotating wire with simultaneous catheter-guided infusion of a liquid sclerosant that irreversibly damages the cellular membranes of the endothelium, causing fibrosis of the vein. The exact mechanism is still not exactly known; however, recent experimental research showed that various sclerosants induced apoptosis in the vein wall rather than having an effect restricted to the endothelium. Incomplete loss of endothelial cells and penetration of the sclerosant effect into the media suggest that medial damage is crucial to the success of sclerotherapy and may explain why it is less effective in larger veins [13]. This poses the question of whether one needs compression post sclerotherapy to improve contact of the sclerosant to the endothelium when media penetration seems to be more important to allow apoptosis of smooth muscle cells.

We, therefore, propose to undertake a randomised study looking at the effect of compression therapy after mechano-chemical ablation using the ClariVein® (www.clarivein.com) device.

## Methods

### Aims

The primary aim of the study is to assess patient’s pain scores for the first 10 days post procedure using a visual analogue scale (VAS). Secondary aims are to compare the two treatment groups with respect to: quality of life scores at baseline, 2 weeks and 6 months using the EQ-5D (EuroQol 5 Dimensions), AVVQ (Aberdeen Varicose Vein Questionnaire) and CIVIQ (ChronIc Venous Insufficiency quality of life Questionnaire) scores; clinical change using the VCSS (Venous Clinical Severity Score) at baseline, 2 weeks and 6 months; the degree of bruising (mild, moderate and severe) and phlebitis at 2 weeks and 6 months; patient compliance with the intervention; time taken to return to work and normal activities; patient satisfaction, assessed with a patient satisfaction questionnaire; and successful obliteration of the target vein, assessed with duplex ultrasound scan at 6 weeks and 6 months. Recanalisation will be defined by a segment of vein ≥ 5 cm. A comparison of the cost-effectiveness of the intervention will also be carried out.

### Study design

This will be a prospective, multi-centre, international randomised controlled trial.

### Study setting

The trial will take place in Singapore General Hospital, Singapore and Roscommon University Hospital, Ireland.

### Target population

Patients referred for treatment of symptomatic varicose veins or chronic venous insufficiency will be recruited if they are found to have primary great saphenous vein (GSV) or small saphenous vein (SSV) incompetence on colour Duplex scan.

### Enrolment criteria

Inclusion criteria for this study include: age ≥ 18 to ≤ 80 years; ability to walk unassisted and ability to attend follow-up visits; and symptomatic GSV or SSV vein reflux > 0.5 s on colour Duplex ultrasound.

Exclusion criteria are as follows: previous or current deep vein thrombosis or pulmonary embolism; patients with a hypercoagulable state; patients on warfarin or novel oral anticoagulants; patients with previous thrombophlebitis in the truncal vein in question, which had recanalised and was now incompetent on duplex ultrasound; recurrent varicose veins (i.e. patients who have had treatment previously in the designated truncal vein with any modality); patients who have had treatment in either leg for an incompetent saphenous truncal vein less than 3 months prior to treatment and enrolment into this study; patients requiring adjuvant treatment of varicose veins; arterial disease (Ankle–Brachial Pressure Index (ABPI) < 0.6 and the absence of a palpable pedal pulse); vein diameter < 3 mm or > 12 mm [14] as measured in the standing position on duplex ultrasound; patients who are unwilling to participate; inability or unwillingness to complete questionnaires; patients unable to provide informed consent or comply with the study protocol; varicose veins unsuitable for MOCA (e.g. very tortuous veins); pregnancy; lycra™ (a type of elastic fabric and fibre used for tight-fitting garments), sclerosant or local anaesthetic allergy; patients who have opted for an alternative method of treatment; patients with a life expectancy less than 12 months; patients with fibromyalgia; patients on anticoagulation with warfarin; and patients with CEAP (Clinical–Etiological–Anatomical–Pathophysiology) Score of C6 (active ulcer) or C1 and C2 (asymptomatic) disease.

### Description of intervention

Patients will be randomised (using computer-generated random numbers in sequentially numbered, opaque, sealed envelopes) to have compression (group A) or no compression (group B). The compression therapy used will be Class II (18–24 mmHg) above-knee compression stockings. Patients randomised to group A will be asked to wear compression stockings for 1 week. This would involve wearing the stocking during the daytime but patients will be allowed to take it off at night whilst in bed. Patients randomised to group B will not be provided with any compression. Those requiring concurrent phlebectomies will be excluded. Patients allocated to compression will all wear the same length, style and grade of stockings.

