In keeping with local preference, patients will be offered the procedure under local anaesthetic (lidocaine 1%) ± sedation. Antibiotics at induction will be routinely given. The patient is positioned supine with a sandbag under the knee to enhance access to the GSV. The SSV can be treated with the patient placed either prone or in the lateral position depending on the surgeon’s preference. A Seldinger technique is used to introduce a micro-catheter 4-F or 5-F introducer sheath into either the great saphenous vein (GSV) or the short saphenous vein (SSV) under ultrasound guidance and flushed with saline. The ClariVein® infusion catheter tip is inserted through the sheath and the tip of the dispersion wire is positioned 20 mm distal to the SFJ, or for the SSV just proximal to the fascial curve. Wire rotation is activated for a 3-s period to induce spasm of the proximal vein prior to commencing pullback. With the wire continuing to rotate, infusion of the sclerosant is started simultaneously with catheter pullback. The activated catheter, which is connected to a 9-V battery-motorised handle, is steadily withdrawn at 1 cm every 7–8 s. The sclerosant used will be 2.0% liquid sodium tetradecyl sulphate (STS) for both the GSV and the SSV. The sclerosant volume used will be 0.1–0.2 ml every 1-cm pullback and will be determined by the vein diameter and overall treatment length. A completion Duplex ultrasound will be performed after the procedure to confirm the patency of the common femoral vein and the deep venous system, and to ascertain whether there is any flow within the truncal vein and whether it is still compressible. The ipsilateral foot will be dorsi-flexed and plantar-flexed in order to minimise deep venous stasis at the end of the procedure [15]. Subcutaneous heparin is routinely given after the procedure to minimise the risk of deep vein thrombosis. A full-length compression bandage (Class II; Coban lite™) will be applied to the treated limb(s) from the foot to the groin. The patient will then be advised to undertake light exercise (3 × 15-min walks on the same day) when they felt well enough to do so. Bandages will be removed in 24 h and patients will be advised to wear compression stockings for 1 week during the daytime if the patient is randomised to the compression arm of the study. Otherwise, the patient will be discharged without compression hosiery.

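### The control arm is said to receive no compression of any kind, yet the procedure section bandages every treated limb for 24 hours, so the document contradicts itself on what is being compared

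*Protocol article*

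**What the plan says.** The protocol article describes the control arm in two places.

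- **Description of intervention** randomises patients to compression (group A) or no compression (group B), as the abstract also does. It specifies the treatment: "The compression therapy used will be Class II (18–24 mmHg) above-knee compression stockings", worn in the daytime for a week. Of the control arm it says: "Patients randomised to group B will not be provided with any compression".
- **ClariVein technique** describes what happens when the procedure ends: "A full-length compression bandage (Class II; Coban lite™) will be applied to the treated limb(s) from the foot to the groin". Next comes: "Bandages will be removed in 24 h and patients will be advised to wear compression stockings for 1 week during the daytime", and that sentence ends by limiting the stocking advice to patients randomised to compression. For everyone else: "Otherwise, the patient will be discharged without compression hosiery".

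The primary aim concerns "pain scores for the first 10 days post procedure using a visual analogue scale", recorded in a daily diary.

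**The concern.** Description of intervention excludes compression of any kind from group B. The technique section gives a compression bandage to all treated limbs. A reader cannot tell from the article what a control patient receives in the first 24 hours.

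Two things are at stake. The first is interpretation: if all patients are bandaged, the result concerns stockings added to a bandage, and a conclusion worded as compression versus none would claim more than the trial tested. The second is consistency of delivery: with one site in Singapore and one in Ireland, each could follow a different section in good faith, and the control regimen would then differ by site.

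**Working it through.** The plan gives no figure on this point, so the check sets the sections side by side and then counts days.

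**Step 1. What depends on allocation.** In the technique section, the sentence applying the bandage stands alone and names no arm. The condition on allocation appears only in the following sentence, with the stocking advice. The closing statement for the other patients withholds hosiery; it does not withhold the bandage. Even if the condition were stretched to cover bandage removal, application would remain unconditional.

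**Step 2. The regimen under each section.**

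| Period | Following Description of intervention | Following ClariVein technique |
|---|---|---|
| First 24 h, group A | No bandage mentioned | Class II bandage |
| First 24 h, group B | Nothing | Class II bandage |
| Stocking week, group A | Daytime Class II stockings | Daytime Class II stockings |
| Stocking week, group B | Nothing | Nothing |
| Comparison | Stockings versus nothing | Bandage then stockings versus bandage alone |

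There is also a hybrid. A site that bandages only group A would compare bandage then stockings with nothing. The text thus admits three different comparisons, and the arm labels do not separate them.

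**Step 3. Does the bandage count as compression in this article's own terms?** Yes. The technique section calls it a compression bandage and grades it Class II, the same class as the stockings. The abstract and Background frame the open question as covering bandages as well as hosiery. It is therefore hard to treat the bandage as outside the thing being studied.

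**Step 4. Diary days affected.** Inputs: a 24-hour bandage, 7 days of stockings, a 10-day diary.

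- Bandage in both arms, stocking week starting at its removal: day 1 alike, days 2–8 different, days 9–10 alike. Days that differ: 10 − 1 − 2 = 7.
- No bandage, stocking week from day 1: days 1–7 different, days 8–10 alike. Days that differ: 10 − 3 = 7.
- Bandage in both arms, stocking week counted from the procedure: days 2–7 different. Days that differ: 6.

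The count of about 7 in 10 therefore comes from a one-week stocking period inside a 10-day diary. The bandage makes day 1 alike in both arms and shifts the contrast; at most it removes one day.

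**The case against.** **The best defence** is that compression here means stockings. Description of intervention defines the therapy that way, and the bandage appears only in the account of the procedure, as if it were care common to both arms. Much of this stands. On that reading the randomised contrast is identifiable and can be estimated without difficulty. It does not rescue the text, because the statement about group B rules out compression of every kind and the bandage is described as compression.

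**Stronger readings that a reader might infer, and why the documents do not support them:**

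- *That the trial cannot answer a useful question.* It can: stockings versus none after a shared bandage is a valid comparison. What fails is the arm label.
- *That the bandage dilutes the primary outcome, so the window should be cut to the days of stocking wear.* Step 4 shows that the bandage is not the main source of the 7-in-10 count. Dilution would also require the pain scores to be averaged over ten days, which the article does not state, and no effect at all on days without a stocking contrast, which it does not state either. Pain after the stockings come off is part of the outcome of the assigned regimen under intention to treat, so a 10-day window is defensible.
- *That power is lost at the planned effect.* Grant both assumptions and keep the SD of the 10-day mean at 20 mm. A 20 mm effect on 7 days then becomes 20 × 7/10 = 14 mm. At the stated 47 per group, 14 / (20 × √(2/47)) = 3.39, and 3.39 − 1.96 = 1.43, which gives power of 92.4%. The 6-day reading gives 12 mm and 82.9%. The figure turns on assumptions that the article does not supply, so it cannot carry a finding.
- *That a null result will be reported as showing compression to be unnecessary.* Nothing in the article says so. The abstract says only that the study may clarify the role of compression.

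**Conclusion.** The contradiction is real and needs correcting: the two sections cannot both be followed for group B. It concerns the first 24 hours after the procedure, about one diary day in ten. Its effect is on the meaning of the comparison: if the technique section is followed, no arm is free of compression, and the estimate is of one week of daytime stockings on top of a 24-hour bandage.

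This rests on the wording of the two sections alone and needs no numerical assumption. The full protocol is not shown and may be clearer, but that would not remove the conflict between two explicit statements in the article. The difference in control regimen between sites is a possibility left open by the text; nothing shows that it will occur.

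**What to change.** 1. Reconcile Description of intervention with ClariVein technique so that the first 24 hours of each arm are described in one way and apply at both sites. Which regimen is right is for the investigators to decide.
2. Name the arms, the aim and the eventual conclusion by the regimens delivered. If the bandage is common to both arms, the statement that group B is given no compression of any kind, and the matching arm label in the abstract, need rewording.
3. Leave the 10-day primary window as it is. A summary of pain over the days on which the regimens differ could be added as a supporting analysis.

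The cost is small. Trial status states that recruitment had not commenced, so these are edits to wording with no effect on data already collected. If the bandage is confirmed for both arms, the price is a narrower claim than compression versus none.
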